### Study blinding

The evaluator will be blinded to the participant’s randomization and allocation sequence. Blinding of participants and therapists will not be possible due to the nature of the study.

### Telerehabilitation group

Participants will follow twice a week, 45-min exercise sessions for 6 weeks via video conferencing guided by a 2-year experienced physiotherapist specialized in traumatology and orthopedics. Participants will receive phone text messages to schedule individual exercises. The patients will be instructed to wear light and comfortable clothes during the exercise sessions.

The telerehabilitation program will be divided into different phases with different goals for the participants. The first phase of the exercise program (first and second weeks) will focus on gaining mobility. The 2nd phase (third and fourth weeks) will focus on cervical and central stabilization. The 3rd phase (fifth and sixth weeks) will focus on muscular resistance improvement of superior and inferior limbs. The descriptions of all the exercises are in Table 1. Exercise will progress by varying the repetitions, load, and a self-rated effort level of at least 5 out of 10 (hard) on a modified Borg Rating of Perceived Exertion scale [41]. In the fifth and sixth weeks, exercise series of 12 to 15 repetitions is expected to be performed with 1 kg and 2 kg objects (dumbbells, water container, others), respectively [32, 42–45].

**Table 1 Tab1:** Description of the telerehabilitation exercise program

Exercise	Description	Series/duration
Stretching (1ª phase)	Sitting position: - Close the hands underneath the base of the head and stretch the cervical flexors by pulling the head forward and down - Put hands under the chin and stretch the cervical extensors by pushing up - Flex the trunk and stretch erector spinal muscles by touching both hands on the ground Upright position: - Put the hand on the opposite head side and stretch the trapezius by hand pulling the head towards the shoulder (then the other hand)	3 series of 30 s with 1-min Interval
Mobilization (1ª phase)	Sitting position: - Actively mobilize the cervical region through flexion, rotation, lateral inclination, and extension movements - Lift the shoulders towards the ears and return to the initial position “Cat-cow” position supported by knees and hands: - Lift the thoracic spine, flex the cervical spine, put the head down, and return to the initial position	2 series of 10 repetitions with 5-s sustain and 1-min intervals
Cervical stabilization (2ª phase)	Sitting position: - Pull the head and chin back - Pull the head back and flex the neck Ventral decubitus position with forearms on the ground: - Extend the trunk and pull the head and chin back	2 series of 10 repetitions with 5-s sustain and 1-min interval
Central stabilization (2ª phase)	Dorsal decubitus position and feet flat on the ground: - Elevate the pelvis until the knees reach 90° - Elevate the pelvis until the knees reach 90° and stretch one leg (then the other leg)	2 series of 10 repetitions with 5-s sustain and 1-min interval
Upper limb resistance (3ª phase)	Upright position: - Hand hold dumbbells down and lift stretched arms forwards from the thighs up the shoulder level; - Hand hold dumbbells down and lift stretched arms forwards from the thighs up the shoulder level; - Flex/extend the elbows holding weight; - Flex elbows by lifting handhold dumbbells up to shoulder level	3 series of 15 repetitions with a 2-min interval
Lower limb resistance (3ª phase)	Sit and stand up from a chair with arms crossed	3 series of 15 repetitions with a 2-min interval

Physical therapists with expertise in traumatology and orthopedics and in the care of patients with spinal diseases carefully prepared the workout program based on the literature. To ensure a more assertive application, the exercise program was subjected to a round of suggestions and modifications from experts in the treatment of patients with spinal pain.

In addition to the exercise program, the participants will receive a digital booklet with self-care information about chronic pain, the benefits of physical exercise, and healthy lifestyle guidelines such as the importance of adequate sleep and nutrition to improve s quality of life.

An online attendance list will be used to track adherence to the exercise program and participants can clarify any doubts regarding the booklet.

### Control group

Participants will receive the same digital booklet with self-care information containing general information about self-management of chronic pain, including pain education, advice on healthy lifestyle and sleeping habits and promotion of physical activity. In addition, participants will receive phone text messages, WhatsApp messages, or e-mails once a week to encourage the maintenance of healthy habits during the study period. The participants will be able to clear doubts through telephone contact. The participants of both groups were instructed not to change any medication prescribed by their physician and not to seek other treatment for their low back pain during the study.

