Telerehabilitation is the use of communication and information technologies such as telephones, video conferencing, sensors, virtual reality, and robotics to deliver rehabilitation services at a distance [15, 16]. This practical modality is becoming popular among patients with musculoskeletal pain as a solution to healthcare access barriers related to travel conditions (distance, transit, transportation) and high demand (long waiting lists) [17–19]. Recent studies indicate that telerehabilitation can improve accessibility to healthcare services and increase patients’ adherence level to exercise programs due to its flexibility and convenience [20–22]. The feasibility of telerehabilitation protocols to treat hip and knee arthroplasty, non-specific low back pain, rheumatoid arthritis, osteoarthritis, and others have been reported [19, 23, 24]. Furthermore, telerehabilitation has been used in a wide range of fields including musculoskeletal pain [25, 26]. Then, high-quality randomized controlled trials are needed to investigate the effectiveness of telerehabilitation for people with neck pain.

A recent study observed that telerehabilitation is an effective method to improve function and relieve pain in patients with musculoskeletal conditions [27]. The only two studies on the effectiveness of telerehabilitation to treat patients with chronic non-specific neck pain have presented methodological flaws such as lack of evaluator blinding, intention-to-treat analysis, and hidden allocation [28, 29]; hence, studies that follow adequate methods are needed.

Therefore, this randomized controlled trial aims to evaluate the effect of a telerehabilitation exercise program versus a digital booklet only with self-care information (chronic pain, benefits of physical exercise, and healthy lifestyle guidelines) in individuals with non-specific chronic neck pain. The primary outcome will be disability at post-treatment (6 weeks) measured using neck pain disability. Secondary outcomes will be pain intensity levels, global perceived effect, self-efficacy, quality of life, kinesiophobia, and adherence to treatment.

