### Eligibility criteria

Potential participants will be phoned to determine eligibility before enrollment:18 to 60 years old male or female interested to treat chronic neck pain.Access to the internet via computer/smartphone.Read and understand the Portuguese language.Neck pain for more than 12 weeks [32].

Individuals with severe musculoskeletal disorders, cardiovascular and metabolic disorders, history of neurological injuries, use of muscle relaxants, obesity (body mass index > 30 kg/m^2^), red flags (unexplained weight loss, fever, moderate to severe trauma, among others) [33], cognitive problems, visual or hearing impairments, or any health condition that hinder safe and proper participation in online exercise sessions will be excluded.

The Physical Activity Readiness Questionnaire (PAR-Q) of the Canadian Society of Exercise Physiology will be used to determine the ability of participants to perform physical activities [34, 35].

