### Primary outcome

Disability will be measured through the Brazilian-Portuguese version of the Neck Disability Index [36], which is a 10-item self-administered questionnaire regarding limitations in daily activities due to neck pain. The total score ranges from 0 (no limitations) to 50 (major limitations) [36].

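### The only restriction on seeking outside treatment names low back pain, in a trial of neck pain

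*Protocol article*

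**What the plan says.** The rule on outside treatment is the last sentence of the Control group section, and it covers both arms. Its first half reads "The participants of both groups were instructed not to change any medication prescribed by their physician". Its second half tells them "not to seek other treatment for their low back pain during the study".

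The sections that define the trial name a different condition. Eligibility criteria requires "Neck pain for more than 12 weeks". Primary outcome describes the Neck Disability Index as a questionnaire about "limitations in daily activities due to neck pain". The title, the aim at the end of the Introduction, and the recruitment section also refer to neck pain.

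The one other mention of low back pain is in the Introduction, in a list of conditions for which telerehabilitation has been reported as feasible: "hip and knee arthroplasty, non-specific low back pain, rheumatoid arthritis, osteoarthritis". That list is background and does not describe this trial's participants.

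**The concern.** The instruction attributes low back pain to participants who were enrolled for something else. A reader can guess the intended word, but this sentence is an operative rule and not background. If it is applied as printed, a participant who starts other treatment for the neck breaks no stated rule, while one who seeks treatment for an unrelated back complaint does.

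Three features of the design make the rule worth getting right:

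- **No participant blinding.** Study blinding states that "Blinding of participants and therapists will not be possible", so participants know which arm they are in.
- **Unequal contact.** One arm has supervised video sessions of 45 minutes twice a week for 6 weeks. The other has a booklet, a weekly message and telephone contact for questions. Participants join because they want their neck pain treated, so those in the control arm have a plausible reason to look elsewhere.
- **Self-reported primary outcome.** The Neck Disability Index is completed by the participant, and outside treatment of the neck could affect it directly.

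The sentence is also in the past tense, so the wording may already have been issued.

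**Working it through.** No arithmetic applies. The check is whether the statements can all describe the same trial, and whether any other sentence supplies the missing rule.

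**Step 1. Which condition does each part of the article name?**

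| Place in the protocol article | Condition named | Role of the text |
|---|---|---|
| Title | Neck pain | Defines the trial |
| Introduction, aim | Neck pain | Defines the trial |
| Study setting and recruitment procedure | Neck pain | Who is approached |
| Eligibility criteria | Neck pain | Who is enrolled |
| Primary outcome | Neck pain | What is measured |
| Introduction, telerehabilitation background | Low back pain, among others | Example from other work |
| Control group, last sentence | Low back pain | Instruction to both arms |

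The phrase low back pain occurs 2 times: 1 as background and 1 as the instruction. Only the instruction ascribes it to this trial's participants, and it conflicts with every part that defines the trial.

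**Step 2. Does another sentence restrict outside treatment for the neck?** None was found. The number of stated restrictions on seeking outside treatment is 1, and that one names the wrong condition.

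**Step 3. What survives of the sentence?** The medication clause, "not to change any medication prescribed by their physician", names no body site. It applies to neck pain on any reading, so what is left open is the seeking of other treatment for the neck.

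**Step 4. Is this an artefact of how the text was read?** No. The sentence is complete, legible prose. It is not part of a table, a redaction or a change log.

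**Step 5. Does the slip affect a stated figure?** No. The sample size rests on a difference of 4.21 points, a standard deviation of 5.58, two-sided alpha of 0.05, 80% power and 15% dropout. None of these depends on the instruction, and correcting the phrase changes none of them.

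**The case against.** The strongest reply is that this is a slip in an English article with no shown consequence.

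- **The article is not the participant text.** Participants must read Portuguese, so what they received was presumably written in that language. An error in the English description says little about that wording, and people seeking care for their neck would most naturally be told about their neck. This stands. It is why the practical consequence can only be stated conditionally.
- **The past tense is weak evidence.** The article uses tense loosely. Statistical analysis, for example, speaks in the past tense of imputation not having been needed, although the analysis has not been run. This also stands. The tense gives a reason to check the participant text, but it does not show that anything was sent.
- **Part of co-treatment is still restricted.** This is correct for prescribed medication, as noted above. The gap concerns only the seeking of other treatment.
- **A question on co-treatment goes beyond the error.** A condensed article may leave the recording of co-interventions to the full protocol or the case report forms. This is fair, and the question is therefore offered below only as an option.

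None of these replies makes the printed sentence right. It still states the trial's only rule on seeking outside treatment for a condition the trial does not study.

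**Conclusion.** The point holds, as a minor inconsistency. One phrase in one sentence is wrong, and that sentence applies to both arms, with 70 participants planned. As printed, the article does not restrict the seeking of other treatment for neck pain in either arm.

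That the phrase was carried over from another text is an inference, though a very probable one. Any harm to the trial depends on the wrong wording having reached participants, which the article can neither confirm nor exclude. No bias in the Neck Disability Index comparison has been shown or estimated. Sample size, alpha and the analysis model are unaffected.

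**What to change.** 1. In the last sentence of the Control group section, replace low back pain with neck pain.
2. Check the instruction actually given to participants. If it does not name neck pain, re-issue it with the same wording in both arms. The channels already exist: for the telerehabilitation arm the article says "Participants will receive phone text messages to schedule individual exercises", and the control arm receives a message every week.
3. Optionally, if the 6-week and 12-week forms do not already ask, add one identically worded question in both arms on other neck treatment and medication change, and report the answers by group. Steps 1 and 2 do not depend on this.

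The cost is a one-phrase correction, a check of one participant text and, if needed, one message to each participant. The optional question adds one item to each follow-up form, which is a small extra burden on participants.

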### Criteria for discontinuing adverse effects and adherence to interventions

The criteria for discontinuation is allowed once a participant requests explicitly or refuses to continue the treatment or follow-up assessment, and the reason will be fully reported. The study will be discontinued in case of serious adverse events (any significant disability, hospitalization, life-threatening, and death) occur that make continuing the study harmful for the participants regardless of if related to the intervention (or control) or not. Ancillary and post-trial care (e.g., provision and/or cover for additional health care of immediate adverse events related to trial procedures) will be provided for participants who suffer sustained harm because of their involvement in this trial at no cost. Even though the study is considered low-risk, patients are encouraged to contact the research team in case of doubts or adverse effects. Moreover, the adherence intervention will be assessed by sending appointment text reminders 30 min ahead of each appointment.

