### Procedure

Eligible participants will receive a digital informed consent form and will be informed about the study objectives by a blinded and trained evaluator. Participants will be referred for baseline assessment consisting of the demographic (age, sex, weight, height, marital state, profession, and education level), clinical (comorbidities, duration of pain, location of pain, average pain intensity, pain area) and medical data. The baseline evaluation will be performed via video conferencing, while the 6-week and 12-week follow-ups will be performed via phone call, smartphone text message, or email by using a Google Forms questionnaire (Fig. 1). All data will be encoded and typed twice using Microsoft Excel. A second blinded evaluator will double-check all data before analysis.

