### Data collection and management plan

Participants will be identified by an individual trial number (ID) to ensure confidentiality, coding, and confidentiality. A data management plan will also be designed in accordance with the recommendations and regulations of the Federal University of Pará, Belem, Brazil. The security and confidentiality of the data collected at all stages will be ensured by storing it on password-protected servers. Paper-based data will be kept in locked filing cabinets at the Postgraduate Program in Human Movement Sciences. Access to the data will be restricted to the lead investigator only. All statistical analyses will be performed using the individual number of each participant and the statistician will be blinded to the group. The results will be presented by group data and any individual data will be spread to ensure confidentiality is preserved.

A Data Monitoring Committee (DMC) will be convened to overview data collection and integrity. The DMC will approve the statistical analysis plan and research protocol. The integrity of trial data will be monitored by regularly scrutinizing data sheets for omissions and errors. Data inconsistencies will be explored and resolved. The lead investigator will be responsible for overseeing trial safety and ensuring that the best interests of participants are observed at all times. The lead investigator will be blinded to allocation, unless unblinding is deemed essential to ensure participant safety. Adverse events will be reported to the reviewing Human Research Ethics Committee and approved requirements.

An adverse incident is defined as a harmful, unpleasant, or undesirable response, reaction, or outcome experienced by a research participant or researcher. Adverse events that may be expected as part of the interventions or usual care that do not need to be reported to the HREC include, muscle soreness, swelling, or muscle cramps related to commencement of unaccustomed exercise or trips and/or falls, that have not resulted in an injury. A serious adverse event is defined as an event that may result in death, be life-threatening, require or prolong inpatient hospitalization, result in persistent or significant disability/incapacity, is a congenital anomaly or birth defect, is some other important medical event, and is expected or unexpected.

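### The only adverse event route described is participant-initiated contact, while live contact during treatment differs by arm (12 sessions against none scheduled), so by-arm counts of non-serious harms may not be comparable

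*Protocol article*

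**What the plan says.** **Route for adverse events.** The section on criteria for discontinuing, adverse effects and adherence says that "patients are encouraged to contact the research team in case of doubts or adverse effects". The wording covers both arms. No other route is described.

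**Contact during treatment.** For the exercise arm, the Telerehabilitation group section says "Participants will follow twice a week, 45-min exercise sessions for 6 weeks via video conferencing", led by a physiotherapist. For the booklet arm, the Control group section says "participants will receive phone text messages, WhatsApp messages, or e-mails once a week to encourage the maintenance of healthy habits", and adds: "The participants will be able to clear doubts through telephone contact".

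**Contact common to both arms.** Under Procedure, "The baseline evaluation will be performed via video conferencing", and "the 6-week and 12-week follow-ups will be performed via phone call, smartphone text message, or email by using a Google Forms questionnaire". The outcome sections list disability, pain, global perceived effect, self-efficacy, quality of life and kinesiophobia. They list no adverse event item.

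**Use made of the events.** The Data collection and management plan section defines adverse and serious adverse events and states: "Adverse events will be reported to the reviewing Human Research Ethics Committee". It exempts some expected exercise-related complaints from that report. The discontinuation section adds a study-level rule: "The study will be discontinued in case of serious adverse events", qualified as events that would make continuing harmful to participants, whether or not they are related to either allocation.

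**The concern.** Spontaneous reporting picks up events in proportion to how easily a participant can mention them. A participant who sees a physiotherapist twice a week has an easy occasion to mention a new headache, a sore shoulder or a clinic visit. A participant with a booklet and a weekly encouragement message has to decide to start a contact. The article's definition of an adverse incident is broad and takes in any unpleasant or undesirable response, so many such events would be too minor to prompt a call.

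Two things are at stake:

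- **Comparison of non-serious harms.** If the trial reports them by arm, the exercise programme could look less safe than the booklet merely because its participants were more often in conversation with staff.
- **Completeness of serious events.** With no prompt at weeks 6 and 12, a hospital admission in either arm could be learned of late or not at all by those who apply the stopping rule. After week 6 this holds equally for both arms, because the live sessions have ended.

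**Working it through.** The documents give no harms figure to reproduce. The check is a count of contacts, followed by an illustration with assumed rates.

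**1. Contacts (from the article)**

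| | Telerehabilitation | Control |
|---|---|---|
| Baseline | live video | live video |
| Scheduled live contact, weeks 1 to 6 | 2 per week × 6 weeks = 12 | 0 |
| Weekly encouragement message | not described | 1 × 6 = 6 over the treatment weeks |
| Weeks 6 and 12 | call, text or email with a form | the same |
| Adverse event item among listed measures | none | none |

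The difference lies in the treatment period. The occasions that the arms share, weeks 6 and 12, carry no stated adverse event question.

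**2. Non-serious events (illustration)**

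Inputs: 70 participants at 1:1 give 35 per arm (Abstract; Randomization and group allocation). Assumed: the same true proportion affected in both arms, 20%; 90% captured under exercise; 30%, 50% or 70% captured under control.

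Expected recorded events = 35 × true proportion × capture.

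- Exercise: 35 × 0.20 × 0.90 = 6.3, or 18% of the arm.
- Control at 30%: 35 × 0.20 × 0.30 = 2.1, or 6%; ratio 0.90/0.30 = 3.0; gap 12 points.
- Control at 50%: 35 × 0.20 × 0.50 = 3.5, or 10%; ratio 0.90/0.50 = 1.8; gap 8 points.
- Control at 70%: 35 × 0.20 × 0.70 = 4.9, or 14%; ratio 0.90/0.70 = 1.29; gap 4 points.
- Control at 90%: 6.3; ratio 1.0; no gap.

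The true proportion cancels out of the ratio, so at 10% or 30% the ratios are the same and only the counts change.

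**3. Serious events (illustration)**

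Assumed true proportion 2%. The chance that at least one event is recorded in an arm of 35 is 1 − (1 − 0.02 × capture)^35.

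- Full capture: 1 − 0.98^35 = 0.51.
- 95% capture: 1 − 0.981^35 = 0.49.
- 80% capture: 1 − 0.984^35 = 0.43.

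The stopping rule looks at both arms together. With full capture in both, the chance of at least one recorded event is 1 − 0.493 × 0.493 = 0.76. With 80% capture in control only, it is 1 − 0.493 × 0.569 = 0.72. The rule is affected far less than a by-arm count of minor events.

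**The case against.** The strongest objection is that one sentence inviting participants to make contact is being treated as the whole method. The article also says that a safety monitoring plan will be followed, and a condensed article may leave case report forms to the full protocol. This stands in part: the text does not say that self-report is the only route. But the article does not leave safety to another document. It sets out definitions, reporting, exemptions and a stopping rule, and the one collection method it states is passive. The point is about that stated choice combined with unequal contact, not about missing detail.

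Second, unequal capture is an inference. No section says that physiotherapists ask about or record events at sessions, and the capture rates above are assumptions. This stands, and it is why the conclusion is that counts could differ, not that they will.

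Third, no by-arm analysis of harms is planned, and harms are not a listed outcome. This stands and limits the consequence to any descriptive account of harms.

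Fourth, the ethics committee exemption for soreness, swelling, cramps and falls without injury removes some of the events most likely to surface only in a session. That narrows the imbalance in that reporting channel. It does not equalise what is collected.

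A reader might also infer three stronger things that the documents do not support:

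- **That control participants are never contacted or asked anything.** They have a live video baseline, weekly messages, telephone access, and follow-ups at weeks 6 and 12 that may be phone calls. The outcome scales also ask both arms about worsening of the neck condition.
- **That the stopping rule is tilted against one arm.** It covers serious events across the whole trial, regardless of cause, and compares no arms.
- **That the efficacy results are compromised.** The efficacy scales are collected in the same way in both arms.

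**Conclusion.** The point holds in a limited form. Participant-initiated contact is the only route described for adverse events, live contact during treatment is 12 sessions against none scheduled, and no common adverse event question is stated at the time points both arms share. A by-arm account of non-serious harms could therefore show an excess under exercise with no true difference behind it. The size is unknown. Under the assumed capture rates the apparent ratio runs from 1.29 to 3.0, and it falls to 1.0 if capture is equal. The direction rests on the assumption that events are mentioned more readily at live sessions.

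For serious events the exposure is to late or missed reports in either arm, and it is small if such events usually come to light anyway. Efficacy estimates and the sample size are untouched. This is a cheap improvement to safety data collection, not a flaw in the main comparison.

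**What to change.** Add the same short structured question to the existing 6-week and 12-week forms in both arms, asking about any new problem, injury, hospital visit or worsening since the last contact. Base any by-arm summary of harms on those answers. List events volunteered at sessions or by spontaneous contact separately, with their source, and do not pool them with the solicited counts. Keep the invitation to contact the team as it is, because it still serves prompt reporting between forms.

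If the full protocol or the safety monitoring plan already contains such a question, one sentence saying so, with its timing and wording, would be enough.

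The cost is one or two items on a form already sent to everyone, and a few extra minor reports to follow up. It should be done before follow-up begins, since unreported events cannot be reliably recovered later.
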